## Abstract

**Background:**

Angiogenesis, among other signaling pathways, plays a key-role in sarcoma biology. Regorafenib (RE) has recently been shown to be effective in imatinib and sunitinib-refractory GIST in a phase III trial.

**Methods/design:**

We are conducting an international trial (France, Austria and Germany) consisting in 4 parallel double-blind placebo-controlled randomized (1/1) phase II trials to assess the activity and safety of RE in doxorubicin-refractory STS (ClinicalTrials.gov: NCT01900743). Each phase II trial is dedicated to one of the 4 following histological subgroups: liposarcoma, leiomyosarcoma, synovial sarcoma and other sarcoma. Within each randomized trial the following stratification factors will be applied: countries and prior exposure to pazopanib. Key-eligibility criteria are: measurable disease, age ≥18, not > 3 previous systemic treatment lines for metastatic disease, metastatic disease not amenable to surgical resection. The primary endpoint is progression-free survival (PFS) according to central radiological review. Secondary endpoints are: Toxicity (NCI-CTC AE V4.0); time to progression; Growth modulation index in pts receiving RE after randomization; 3 and 6 months PFS-Rates, best response rate and overall survival. Each phase II trial will be separately analyzed. In 3 trials, statistical assumptions are: PFS0 = 1.6 & PFS1 = 4.6 months; 1-sided α = 0.1; β = 0.05 with a total sample size of 192 pts. To take into account the rarity of synovial sarcoma, the statistical assumptions are: PFS0 = 1.6 & PFS1 = 4.6 months; 1-sided α = 0.1; β = 0.2 Tumor assessment is done monthly during the 4 first months, and every 3 months thereafter. After central radiological confirmation of tumor progression, an optional open-label option is offered to eligible patients.

**Discussion:**

The design of this trial allows an assessment of regorafenib activity over placebo in four sarcoma strata and might provide evidence for launching a phase III trial. This study includes both integrative and exploratory translational research program. The study is enrolling since June 2013 (Trial Registration Number: EudraCT N°: 2012-005743-24, on the 15^th^ February 2012).

## Background

### Clinical setting

Soft tissue sarcomas (STS) are a heterogeneous group of tumor, accounting for at least 2% of adult cancers. Soft tissue sarcoma comprises more than 50 different histological subtypes. The 4 major subgroups are: liposarcoma, leiomyosarcoma, synovial sarcoma and other sarcomas. Despite large en bloc resection plus radiotherapy more than 40% of patients experience metastatic recurrence. For patients with advanced disease, palliative chemotherapy based on doxorubicin (+/- ifosfamide) represents the standard of care. Doxorubicin provides a response rate of about 20% and a median overall survival of about 12-18 months [1,2]. Today, there is no consensual treatment after intolerance or failure of doxorubicin. Nevertheless, some new drugs provide promising signs of activity (trabectedin, gemcitabine-docetaxel, pazopanib, eribuline … [2-5]), but until now, none of them could be considered as a standard of care after doxorubicin-failure or intolerance. Main subtypes of soft tissue sarcoma are: liposarcoma (25-30%), leiomyosarcome (25-30%) and synovial sarcomas (10%). Angiogenesis is of crucial importance for growth and dissemination of malignancies. In this process vascular endothelial growth factors and other pro-angiogenic factors are of major importance. There is a large body of evidence that angiogenesis plays a key-role in the development of sarcomas [6-13].

Moreover, one of the promising drugs for the treatment of STSs, pazopanib is an oral angiogenesis inhibitor with activity against vascular endothelial growth factor receptors (VEGFR) 1, 2 and 3, and platelet-derived growth factor receptor (PDGFR) [5]. Excluding liposarcomas, pazopanib improves the PFS over placebo [14].

### Investigational treatment

Regorafenib (BAY 73-4506) is an orally bioavailable multikinase inhibitor targeting tumor cells, vasculature, and the tumor microenvironment. Regorafenib (BAY 73-4506) binds to and inhibits VEGFR-1, - 2 and -3, and tumor cell signaling kinases (RET, KIT, PDGFR, and Raf), which may result in the inhibition of tumor angiogenesis and tumor cell proliferation. Regorafenib (BAY 73-4506) shows potent, oral activity in a wide variety of preclinical xenograft models. Regorafenib has completed a first set of phase I- III clinical trials [15,16]. In the phase I trial, one of the three responding patients had had an advanced sarcoma [15].

### Prior experience with regorafenib

Regorafenib showed efficacy and manageable toxicity in the treatment of refractory colorectal cancers (CRC) and GIST in two phase III trials.

The CORRECT study was an international, multicenter, randomized, double-blind, placebo-controlled Phase III study that enrolled 760 patients with mCRC whose disease had progressed during or within 3 months following last administration of approved standard therapies, which included a fluoropyrimidine, oxaliplatin, irinotecan, bevacizumab and cetuximab or panitumumab. Patients who had withdrawn from standard treatment due to unacceptable toxicity warranting discontinuation of treatment and precluding retreatment with the same agent prior to progression of disease were also allowed into the study. Patients were randomized to receive either regorafenib plus best supportive care (BSC) or placebo plus BSC. Treatment cycles consisted of 160 mg of regorafenib (or matching placebo) once daily for three weeks on/one week off. The study met its primary endpoint, showing statistically significant improvement in overall survival (OS) by 29% (HR = 0.77, p = 0.0052, median OS: 6.4 months vs. 5.0 months for the placebo group) in patients with metastatic colorectal cancer (mCRC) whose disease had progressed after approved standard therapies. Additionally, findings from the secondary endpoints of the CORRECT study showed statistically significant improvement in progression-free survival (PFS) (HR = 0.49, p < 0.000001, median PFS: 1.9 months vs. 1.7 months) and an improvement in disease control rate (44.8% vs. 15.3%) in patients treated with regorafenib compared to those treated with placebo. The most common drug-related, treatment-emergent adverse events included fatigue (47.4% vs. 28.1%), hand-foot skin reaction (46.6% vs. 7.5%), diarrhea (33.8% vs. 8.3%), anorexia (30.4% vs. 15.4%), hypertension (27.8% vs. 5.9%), oral mucositis (27.2% vs. 3.6%) and rash/desquamation (26.0% vs. 4.0%) for patients receiving regorafenib as compared to placebo [17]. Regarding these findings, regorafenib is now approved for the treatment of mCRC in USA, Europe, and many other countries.

GRID was a randomized, double-blind, placebo-controlled, multi-center, Phase III study of regorafenib for the treatment of GIST. It enrolled 199 patients whose disease had progressed despite prior treatment with imatinib and sunitinib. Patients were randomized in a 2:1 ratio to receive either regorafenib (160 mg once daily, three weeks on/one week off) plus BSC or placebo plus BSC to evaluate efficacy and safety. The primary endpoint of this trial was PFS, and secondary endpoints included overall survival, time to progression, disease control rate, tumor response rate, and duration of response. The GRID study met its primary endpoint of progression-free survival (PFS) (HR = 0.27, p < 0.0001). The median PFS was 4.8 months in the regorafenib arm vs. 0.9 months in the placebo arm. The most common drug-related, treatment-emergent adverse events (occurring in at least 10% of patients during double-blind treatment) included hand-foot skin reaction (56.1% vs.15.2%), hypertension (48.5% vs. 16.7%), diarrhea (40.9% vs.7.6%), fatigue (38.6% vs. 27.3%), oral mucositis (37.9% vs. 9.1%), alopecia (23.5% vs. 3.0%), hoarseness (22.0% vs. 4.5%), anorexia (20.5% vs. 7.6%), maculopapular rash (18.2% vs. 3.0%), nausea (15.9% vs. 9.1%), constipation (15.2% vs. 7.6%), myalgia (13.6% vs. 9.1%), and voice alteration (11.4% vs. 3.0%) for patients receiving regorafenib as compared to placebo [18]. Regarding this findings regorafenib in now approved for the treatment of GIST in USA and European countries.

### Rationale for the study

The standard of care for metastatic STSs is doxorubicin +/- ifosfamide. After failure or intolerance to doxorubicin, there is no standard of care. In Europe, two drugs are currently approved for the treatment of soft tissue sarcoma after failure/intolerance to doxorubicin: trabectedin (Yondelis ®) for all histological subtype and pazopanib (Votrient ®) for all subtypes excluding liposarcomas. Trabectedin is mostly active in liposarcoma and leiomyosarcoma. Pazopanib is active in non-lipomatous sarcomas. New treatments are needed for the various histological STS subtypes; an unmet medical need so far.

The study population is represented by patients with metastatic STS having received at least doxorubicin (or other anthracyclin) as a previous therapy line. Patients will have measurable disease by Response Evaluation Criteria in Solid Tumors (RECIST 1.1) and will have documented disease progression according to RECIST within the last 6 months before entry in the study, after treatment with doxorubicin (or other anthracyclin derivatives). The study consists of 4 parallel randomized phase II trials, defined by the 4 following histological subgroups: liposarcoma, leiomyosarcoma, synovial sarcoma and other sarcomas (according to local histology).

## Methods/Design

### Study objectives

The primary objective of the trial is to investigate, in each of the 4 parallel studies, whether treatment with regorafenib improves progression-free survival as compared to placebo.

The secondary objectives include other efficacy outcomes and an evaluation of the tolerance/toxicity of regorafenib in the study population. A translational program research is part of the study (see below).

### Study endpoints

The primary endpoint of this phase II study is progression-free survival (PFS) according to modified Response Evaluation Criteria in Solid Tumors (RECIST 1.1) with central radiological review. Progression-Free Survival will be measured from the date of randomization until the date of radiological progression or death of any cause (whatever occurs first). Patients without tumor progression or death at the time of analysis will be censored at their last date of radiological tumor assessment. The date of disease of progression will be the date of first observation of progression (primary analysis on intent-to-treat analysis, according to RECIST 1.1 guidelines and central radiological review).

The secondary endpoints are the following:Disease Control Rate (DCR),Disease Control Rate is defined as the proportion of patients who have a best response rating of complete response (CR), partial response (PR) or stable disease (SD) according to RECIST guidelines 1.1 that is achieved during treatment or within 30 days after termination of study medication. Stable disease must be at least 6 weeks in duration.Time To Progression (TTP),Time to progression will be measured from the date of randomization to the date of the first progression. Patients who die from causes other than progression are censored at the date of death.Tumor Response Rate (RR)Tumor Response Rate is defined as the proportion of patients with the best overall tumor response of partial response (PR) or complete response (CR) according to RECIST 1.1 guidelines that is achieved during treatment or within 30 days after termination of study medication.Duration of response,Duration of response is measured from complete or partial response to progression or death.Overall survival (OS),Overall Survival is measured from the date of randomization until the date of death due to any cause.Growth Modulation Index (GMI)The Growth modulation index is defined as the ratio of time to progression under regorafenib to time to progression under previous treatment. The growth modulation index will be explored in patients receiving regorafenib after randomization [18].ToxicityToxicity will be evaluated according to NCI-CTC AE V4.0

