### Overview of the study design

This is an international trial consisting of 4 parallel randomized, double-blind, placebo-controlled, multi-center phase II studies to evaluate the efficacy and safety of regorafenib in patients with histologically proven metastatic and/or unresectable STS after failure or intolerance to doxorubicin (or other anthracyclin). Patients must have shown objective disease progression at study entry.

Patients will be registered at the Clinical Research Unit of the Oscar Lambret Cancer Center prior to start the treatment, and after verification of eligibility criteria. Patients will be randomized to receive oral regorafenib or placebo in a 1:1 ratio, until disease progression (RECIST 1.1 guidelines), death, unacceptable toxicity or withdrawal of consent for any reasons. Patients receiving placebo who experience disease progression may be offered open-label regorafenib after checking of eligibility criteria and real-time central radiological review of imaging to confirm progression according to RECIST 1.1 (Figure 1).

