**Trial Design: 4 parallel phase II double-blind placebo-controlled phase II trials.**

An independent data monitoring committee is planned to assess the risk/benefit ratio after enrollment of the 50 first patients.

The study is composed of 3 periods:Screening PeriodTreatment Period during which either regorafenib or placebo will be administered (The Treatment Period includes an end of treatment visit and a 30 (+/-7) day follow-up period that ends with a safety follow-up visit).Survival Follow-up Period during which survival status will be monitored

During the Screening Period and the Treatment Period, patients are considered “on-study”; during the Survival Follow-up Period, patients are considered “off-study”. During the treatment period the tumour assessment will be done every month during the 4 first months and then every 3 months. Study assessments is summarized in Table 1 (Flow-chart).

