**Table 1 Tab1:** **Study procedures and flow-chart**

	Screening 14 days	d1, d30, d60, d90, d120	After the 4^th^month, every 3 months until tolerance or progession
Physical exam	X	X	X
Safety	X	X	X
Availbility of tumour sample	X		
Thoracic and abdominopelvic CT-Scann	X	X	X
Echocardio or MUGA	X		X
Hematology INR TCA	X	X	X
Biochemistry (1)	X	X	X
Urine Dipstick	X	X	X
Serum sample for TR programm		X	

(1) Serum creatinine, Glomerular filtration rate (Cockroff and Gault), AST, ALT, Bilirubin, Alkaline phosphatases, Amylase and lipase, CPK.

The patients will be randomly allocated to one of the treatment described above.Regorafenib: 4 tablets, once daily, 3 weeks on/1 week off

+ Best Supportive Care

OrPlacebo: 4 tablets, once daily, 3 weeks on/1 week off

+ Best Supportive Care

until progression or unacceptable toxicity in both arms.

Best supportive care includes any method to preserve the comfort and dignity of the patients and excludes any disease-specific anti-neoplastic agent.

Details on dose-adaptations, prohibited concomitant medications and the study flow-chart could be obtained by request to the corresponding author.

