#### Statistical analysis

Progression free survival will be analyzed in the intent to treat population. For the primary analysis, in each stratum, a one sided logrank test stratified for pre-specified stratification factors will be used, and tested at the significance level of 0.10. The size of the treatment difference will be measured by the estimated hazard ratio and its 95% confidence interval.

The progression free survival rates will be estimated as a function of time by the Kaplan-Meier method. Overall survival will be analyzed in the intent to treat population. The overall survival rates will be estimated as a function of time by the Kaplan-Meier method. Time to progression rates will be estimated as a function of time by the Kaplan-Meier method in the intent to treat population. Response rates at 3 and 6 months, progression-free rates at 3 and 6 months will be analyzed by descriptive techniques (intent to treat analysis).

The occurrence of adverse events will be analyzed in the safety population, by descriptive techniques. For each type of adverse event, the worst grade observed across the whole therapy will be tabulated by treatment arm, and the percentages of grade 2+ and grade 3+ cases will be provided. For events occurring in more than 10% of the cases at a grade 2+, the cumulative incidence will be computed as a function of time for each grade, by treatment arm, considering discontinuation of therapy for reasons other than an adverse event as a competing risk.

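### TTP is censored at the date of death for non-progression deaths, although scans are scheduled only during treatment, so unscanned months count as progression-free time

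*Protocol article*

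**What the plan says.** All references are to the protocol article.

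- **TTP definition and censoring (Study endpoints).** "Time to progression will be measured from the date of randomization to the date of the first progression". Then: "Patients who die from causes other than progression are censored at the date of death".
- **TTP analysis (Statistical analysis).** "Time to progression rates will be estimated as a function of time by the Kaplan-Meier method in the intent to treat population". No test of TTP is stated.
- **When scans are done (text under the Trial Design figure title).** "During the treatment period the tumour assessment will be done every month during the 4 first months and then every 3 months". The last column of Table 1 runs "every 3 months until tolerance or progession", and no imaging column follows it.
- **What is followed afterwards (same text).** "Survival Follow-up Period during which survival status will be monitored".
- **How treatment can end (Overview of the study design).** Treatment runs "until disease progression (RECIST 1.1 guidelines), death, unacceptable toxicity or withdrawal of consent for any reasons", so it can end without progression.
- **PFS censoring, for comparison (Study endpoints).** "Patients without tumor progression or death at the time of analysis will be censored at their last date of radiological tumor assessment". Death from any cause is itself a PFS event.

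TTP under regorafenib is also the numerator of the growth modulation index (Study endpoints).

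**The concern.** TTP counts only progression, and progression can be seen only while scans are being done. Take a patient with stable disease who stops for toxicity at month 2 and dies of another cause at month 10. As written, TTP is censored at month 10, so 10 − 2 = 8 months without a scheduled scan count as time at risk and free of progression.

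Such time adds patients to the risk set but cannot add events. The estimated progression rate falls and the TTP curve rises. In the growth modulation index, the same patient enters with a censored numerator of 10 months instead of 2. What is at stake is the accuracy of one secondary endpoint and of an exploratory ratio, in strata of about 25 patients per arm (about half that in synovial sarcoma).

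**Working it through.** **1. The plan's own figures.** The article gives no figure for TTP, non-progression deaths or toxicity stops. Its event counts are for PFS, with medians of 1.6 and 4.6 months and one-sided alpha 0.10. The Schoenfeld formula with 1:1 allocation is d = 4(z₁₋α + z₁₋β)² / (ln HR)², with HR = 1.6/4.6 = 0.348. It gives 30.7 events at power 0.95 (stated: 30) and 16.2 at power 0.80 (stated: 16). These agree to within rounding. TTP does not enter them, so no sample-size figure depends on this point.

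**2. Direction.** The Kaplan-Meier estimate is S(t) = ∏(1 − dⱼ/rⱼ) over the progression dates. Moving a censoring date from the last scan to a later death leaves every dⱼ unchanged and can only enlarge later rⱼ. Each factor stays the same or grows, so within an arm S(t) cannot fall.

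**3. Deaths on treatment.** If a patient dies between two scheduled scans, both rules keep the patient in the risk set at the last scan and remove the patient before the next. When progression dates fall on the scan grid, the estimate is identical.

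**4. Size when patients stop early.** Simulation with 20,000 patients per arm:
- Exponential TTP with the plan's PFS medians (4.6 and 1.6 months) used as TTP medians.
- Scans at months 1, 2, 3 and 4, then every 3 months; none after a non-progression stop; 18 months of follow-up.
- All stop and death rates are assumptions, given as 6-month probabilities.

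As a check of the model, the formula S(t) = 2^(−t/median) gives 2^(−7/4.6) = 0.348 on regorafenib at month 7. The simulation without stops gives 0.349.

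| Assumed rates (regorafenib/placebo) | Affected per 25 | Regorafenib 7-month estimate: at death vs last scan | Rise in points, regorafenib/placebo | HR: at death vs last scan |
|---|---|---|---|---|
| No stops; 3% on-treatment deaths | 0.9/0.4 | 0.349 vs 0.349 | 0/0 | 0.355 vs 0.355 |
| Mild: stops 10%/3%, on-treatment deaths 2%, off-treatment 20% | 1.6/0.5 | 0.365 vs 0.350 | 1.5/0.4 | 0.352 vs 0.354 |
| Moderate: stops 20%/5%, on-treatment deaths 3%, off-treatment 30% | 3.6/0.7 | 0.388 vs 0.348 | 4.0/0.9 | 0.347 vs 0.360 |
| Extreme: stops 30%/5%, on-treatment deaths 5%, off-treatment 50% | 7.0/1.1 | 0.435 vs 0.354 | 8.0/1.1 | 0.308 vs 0.347 |
| Equal: stops 15%/15%, on-treatment deaths 3%, off-treatment 30% | 2.9/1.5 | 0.380 vs 0.352 | 2.9/2.9 | 0.392 vs 0.356 |

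All deaths in the table are from causes other than progression.

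**5. Median.** It was 7 months on regorafenib and 2 months on placebo under both rules in every row. The grid explains this. On regorafenib S(4) = 2^(−4/4.6) = 0.547 and S(7) = 0.348, so the curve crosses 0.5 at the month-7 scan. On placebo S(1) = 2^(−1/1.6) = 0.648 and S(2) = 2^(−2/1.6) = 0.420, so it crosses at month 2. The shifts in the table are too small to carry either crossing to another scan.

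**The case against.** **Scans may in fact continue.** The article nowhere says that imaging stops for a patient who leaves treatment without progression. It is a condensed account, and it offers further flow-chart details on request. If scans continue to progression, censoring at death is a coherent choice for TTP. This stands as a limit on the point. Still, all the text shown points the other way: assessments are tied to the treatment period, Table 1 has no later imaging column, and follow-up is of survival status alone.

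**The rule affects few patients.** It applies only to deaths from other causes. In progressing metastatic sarcoma, many patients who stop for toxicity would later progress or die of sarcoma, and the rule does not touch them. With 12% of patients assigned a toxicity stop between months 1 and 4, a 4.6-month median and the scan grid, the regorafenib 6-month rate rises by 1.7 to 2.1 points if every patient who stops before progression dies of another cause (mean 3 or 8 months after stopping). It rises by 0.5 to 0.7 points if 30% do. This stands, and it keeps the likely effect small.

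**Stronger readings that a reader might infer, and that the documents do not support:**
- *That the TTP and PFS rules contradict each other.* The PFS censoring rule covers only patients with neither progression nor death. In the example above PFS is an event at month 10, and TTP is censored on the same date.
- *That the rule mainly favours regorafenib.* This needs more non-progression stops on that arm. The colorectal and GIST trials summarised in the Background show more drug-related adverse events on regorafenib, which makes it plausible, but no stop rates by arm are given for this trial. With equal stop rates both curves rose by 2.9 points and the hazard ratio moved against regorafenib.
- *That median TTP is inflated.* A continuous-time calculation that ignores the scan schedule suggests a rise from 4.6 to between 4.8 and 5.2 months. On the planned grid the median does not move.

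**Conclusion.** The point holds as a small defect in a secondary endpoint. On the text shown, the TTP rule counts months without scheduled imaging as progression-free time at risk, and this can only push an arm's Kaplan-Meier TTP estimate upwards.

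The effect is nil for on-treatment deaths alone. It is about 1.5 to 4 points on the regorafenib 7-month estimate under mild to moderate assumed rates. The 8-point case needs extreme rates and should not be taken as an expectation. The effect on the hazard ratio has no fixed direction.

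These sizes rest on assumed stop and death rates, exponential times, PFS medians standing in for TTP, and no scans after a non-progression stop. They are large-sample values; a stratum of about 25 per arm will vary around them. The primary PFS analysis and the sample size are unaffected.

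**What to change.** Replace the TTP censoring sentence with: patients who die of causes other than progression, without documented progression, are censored at their last evaluable radiological tumour assessment before death. For these patients the date will differ from PFS, where the death remains an event at its own date; the text should say that this is intended.

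If scans do continue to progression after treatment stops, state that in the assessment schedule and keep the present rule.

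Either change is one sentence and needs no new data. The cost of the first is slightly shorter TTP estimates and slightly less follow-up time.

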### Methodological discussion

The writing committee had faced to 2 major issues: (i) the vast heterogeneity of STS in terms of histologies and prior treatments, (ii) the absence of standard of care in this setting and (iii) the choice of the primary endpoint. The proposed trial design is a complex one, integrating randomization, stratification and the application of 4 parallel placebo-controlled randomized phase II trials. This could be discussed point by point.

Most of phase II trials assessing the activity of a new drug in STS are not randomized. There at least 2 reasons justifying the randomization: the choice of placebo as internal comparator and the choice of the primary endpoint. Non-randomized phase II trials are exposed to selection biases related to the respective eligibility criteria. Thus, the use of an internal comparator is helpful to ensure the representativity of enrolled patients. The major issue here is the choice of the comparator. The list of potential comparators is vast, including dacarbazine, gemcitabine, pazopanib, trabectedin … There is no consensual treatment. To avoid never-ending discussion about the optimal choice of the comparator (including “physician choice”), we have decided to use placebo as internal comparator to provide a clear-cut estimate of the drug activity.

Most of phase II trials in STS patients run a fixed-time point primary endpoint (such as 3-month progression-free rate or 6-month progression-free rate). Because tumour shrinkage is rare with such kinds of drugs and especially in case of STS, tumor response is an inadequate primary endpoint. Some other endpoints could be used (Choi criteria, functional imaging such as contrast enhanced ultrasonography or position emission tomography), but none of these criteria is formally validated and standardized in this setting. In this case, we have to measure how the investigational drug slows down the tumor course [19]. As a consequence, because we have used a time-dependent endpoint (PFS), randomization is absolutely necessary. Without randomization, impact on PFS could have been related to the natural history of STS or the drug activity.

Heterogeneity in term of prior management of STS had also to be taken into account. As a consequence, we have used 2 stratification factors in each parallel phase II trials: prior exposure to pazopanib and countries.

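### The growth modulation index is explored only in regorafenib recipients, so this secondary endpoint lacks the concurrent randomised control that the placebo arm could supply (low priority)

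*Protocol article*

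**What the plan says.** In the protocol article, under Study endpoints, the index is set out in two sentences: "The Growth modulation index is defined as the ratio of time to progression under regorafenib to time to progression under previous treatment" and "The growth modulation index will be explored in patients receiving regorafenib after randomization". The Methods/design part of the abstract names it among the secondary endpoints with the same restriction: "Growth modulation index in pts receiving RE after randomization".

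Other parts of the article bear on how it is read:

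- **TTP (Study endpoints).** "Time to progression will be measured from the date of randomization to the date of the first progression". TTP is also a secondary endpoint in its own right, and under Statistical analysis it is estimated by Kaplan-Meier in the intention-to-treat population.
- **Scans (below the Figure 1 caption).** "During the treatment period the tumour assessment will be done every month during the 4 first months and then every 3 months". This applies to both arms.
- **Entry.** Rationale for the study and Overview of the study design require documented progression before entry, whichever arm is then allocated.
- **Crossover (Overview of the study design).** "Patients receiving placebo who experience disease progression may be offered open-label regorafenib". Pre-planned sensitivity or exploratory analyses gives these data a separate descriptive analysis and lists its outcomes. The index is not among them.
- **Why the trial is randomised (Methodological discussion).** "Without randomization, impact on PFS could have been related to the natural history of STS or the drug activity".

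**The concern.** A ratio of successive times to progression compares a patient with his or her own past. That past is a real reference, but it differs from the trial period in more than the drug: the disease is at a later stage, the patient was selected for recent progression, and the scan interval may have changed. A single-arm distribution of the ratio mixes all of these with the drug effect.

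The trial already holds the group that would separate them. Placebo patients are randomised concurrently, have the same entry requirement and are scanned on the same schedule. For each of them, on-study TTP can be divided by TTP on the last line before randomisation. Restricting the index to regorafenib recipients leaves that comparison out. What is at stake is the interpretation of one secondary endpoint: a reader who meets a high or low share of ratios above 1 has no yardstick in the trial for what that share would have been without the drug.

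**Working it through.** **Plan's own figures.** The article gives no figure for the index. Its design medians are PFS medians: 1.6 months on placebo and 4.6 on regorafenib (Statistical hypothesis – Sample size calculation). They are consistent with the stated event numbers. With HR = 1.6/4.6 = 0.348, ln HR = −1.056 and one-sided alpha 0.10, Schoenfeld's formula 4(z_α + z_β)²/(ln HR)² gives:

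- power 0.95: 4(1.2816 + 1.6449)²/1.1153 = 30.7, against 30 stated;
- power 0.80: 4(1.2816 + 0.8416)²/1.1153 = 16.2, against 16 stated.

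These concern the primary comparison. They serve here only to confirm the medians used below.

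**Assumptions not in the documents.** TTP is exponential, the PFS medians stand in for TTP medians, and the median TTP on the prior line lies between 1.6 and 4.6 months. The correlation between a patient's two times is 0 or 0.5 (Gaussian copula).

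**Share of patients with a ratio above 1.** For independent exponential times with on-study median m₁ and prior median m₂, P(ratio > 1) = m₁/(m₁ + m₂). For example, 4.6/(4.6 + 1.6) = 0.742 and 1.6/(1.6 + 4.6) = 0.258. The values at correlation 0.5 are simulated.

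| Prior median (months) | Correlation | On-study median 1.6 (placebo, or inert drug) | On-study median 4.6 (full assumed effect) |
|---|---|---|---|
| 1.6 | 0 | 0.50 | 0.74 |
| 3 | 0 | 0.35 | 0.61 |
| 4.6 | 0 | 0.26 | 0.50 |
| 1.6 | 0.5 | 0.50 | 0.82 |
| 3 | 0.5 | 0.29 | 0.65 |
| 4.6 | 0.5 | 0.18 | 0.50 |

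**Reading the table.** A regorafenib-only result of 50% appears twice: with an inert drug when the prior median is 1.6, and with the full assumed effect when the prior median is 4.6. Correlation does not change this, because two times with the same distribution and symmetric dependence give 50% by symmetry.

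With a placebo ratio alongside, the two cases part. In the first, both arms show 50%, a difference of 0. In the second, regorafenib shows 50% and placebo 26% (correlation 0) or 18% (correlation 0.5), a difference of 24 or 32 percentage points. Randomisation makes the prior-TTP distribution the same in expectation in both arms, so a difference between arms reflects the on-study period.

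**Scan schedule.** Suppose true TTP has the same distribution on both lines. Round the on-study time up to months 1, 2, 3, 4, 7, 10 and so on, and the prior time up to an assumed 2- or 3-monthly grid. For true medians of 2.5 to 4 months, the geometric mean of the ratio is 0.83 to 0.90 (2-monthly) and 0.69 to 0.78 (3-monthly). With prior scans every 1.5 months and medians of 4 to 4.6 months it is 0.97 to 0.98. Under these assumptions the effect lowers the index, by an amount that depends on a prior schedule the documents do not give. Within the trial both arms share one schedule, so a comparison between arms is free of this imbalance.

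**The case against.** The strongest reply is that nothing rests on the index. It is only explored, with no test, threshold or decision rule, and drug effect is judged in each stratum by the one-sided log-rank test of PFS against placebo. The sentence in the Methodological discussion justifies randomising for PFS, and the plan does randomise. A randomised contrast in TTP is also available, since TTP is estimated in the intention-to-treat population. On this view a two-arm ratio is a further endpoint, and its absence is no misstatement. The points on weight stand and set the priority. They do not supply what the index itself lacks: the article fixes its population in a way that leaves the randomised comparison unused.

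Three stronger readings are tempting and are not supported.

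- **That the index has no control at all.** Each patient's prior TTP is a reference. Only a concurrent randomised control is missing.
- **That crossed-over placebo patients are counted, with placebo as their previous treatment.** Read literally, the population wording could admit them. But crossover data have their own analysis, which does not list the index, and TTP runs from randomisation to first progression, which for these patients occurs on placebo. The article nowhere calls placebo a previous treatment. Excluding these patients would not create a control either, so the two matters are separate.
- **That unequal scan intervals inflate the index.** In the cases worked above they lower it or leave it nearly unchanged.

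How censoring is handled may be settled in the full protocol or analysis plan, and its absence from an article is no finding.

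**Conclusion.** The point holds in a limited form. As fixed in the article, the index compares regorafenib recipients with their own earlier treatment only, and alone it cannot tell drug effect from disease course or a changed scan schedule. The article's own argument for randomising applies to it.

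The size is illustrative: across prior medians of 1.6 to 4.6 months, the share above 1 runs from 18% to 50% with no drug effect and from 50% to 82% with the full assumed effect, so the ranges meet at 50%. This rests on exponential times, PFS medians used for TTP, and assumed prior medians and correlations.

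It would go too far to conclude that the endpoint is uninterpretable or that the trial's conclusion on activity is weakened. The index remains a valid within-patient description, and the primary comparison does not depend on it. This is a low-priority, nearly free improvement.

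**What to change.** Compute one ratio in both randomised arms: TTP in the blinded phase, counted from randomisation, divided by TTP on the last systemic line before randomisation. Report the two arms side by side, with the proportion above 1 and the distribution, and handle censored on-study times, for instance by a Kaplan-Meier estimate of the ratio.

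Word the population as patients randomised to regorafenib and patients randomised to placebo. Keep open-label regorafenib after crossover in the separate descriptive analysis already planned.

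The cost is a change of wording, one extra table, and the treatment-history dates of the last prior line for placebo patients. No further patients, scans or procedures are needed. If the placebo ratio is not wanted, the minimum is to label the index as descriptive and not to attribute its result to the drug.
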